### 8.3 Criteria for discontinuing study participation

The patient will be withdrawn from the study if he withdraws his consent to participate in the study. Details of participant withdrawal must be documented in the source document and eCRF. Upon withdrawal from the study, drug treatments will be determined by the patient's assistant physician. The patient may withdraw his consent to participate in the study for any reason and at any time, without prejudice to the continuity of his medical care.

The request to withdraw consent means that the patient no longer wants to participate in the study, that is, does not want to be evaluated and monitored in the study, perform any procedures related to the study, or be contacted again by the research team. Furthermore, further analysis of previously collected biological materials will not be allowed. In this situation, the study team will only contact the participant to withdraw the study medication. Local investigators must document withdrawal of patient consent and inform the Coordinating Center. Patients who withdraw consent

and discontinue their participation in the study after randomization will not be replaced by other participants.

Randomized patients may also refuse to participate in specific aspects of the study or refuse to continue using the proposed drugs, without withdrawing their consent to participate. In this case, patients should be asked for permission to continue to follow them until the end of the study. Local investigators must make every effort to accommodate the needs of patients to maintain their participation in the study.

It is reinforced that only patients with a positive diagnosis of COVID-19 will be included in the study. However, after randomization (D1), the RT-PCR test will be collected from all participants, necessary for standardizing the test and collection to obtain the viral load of SARS-CoV-2 on the day of inclusion in the study. Although the false-negative rates for rapid tests and RT-PCR that confirmed the diagnosis of COVID-19 in participants (prior to inclusion) are low, it is possible that the participant will have a positive test at the time of inclusion and a negative test. In the first collection of the study (D0). In this circumstance, the participant will no longer receive the proposed treatment, and additional clinical and laboratory data will not be collected.

#### 8.4 Risks and discomforts

There is a risk of breach of confidentiality of information collected from research participants. This risk is inherent in any research, and is not greater in the present research. To mitigate these risks, the records of participation in this study will be kept confidential and will be accessed in a restricted way only by people linked to the study, who will transfer the clinical information to specific forms (which do not have information that can identify the research participant) and verify that the study is being carried out properly. Only a number generated at the beginning of the study, the initials and / or date of birth will be used to identify the participant. The confidentiality and privacy of all information will be ensured.

There may still be some risk of embarrassment, however, the study team is trained to approach the participant in a way that does not cause any malaise or discomfort of this type, always thinking about the participant's well-being and freedom.

The electronic data collection form will identify the patient and the investigating center by the corresponding number. The data obtained from the medical record must be kept confidential by the investigator centers, in lockers with restricted access and the guarantee of anonymity of all data in provisional and definitive reports will be ensured.

Other potential risks to the research participant are related to the collection of biological samples. Regarding blood collections, these do not differ from collections for routine exams. Thus, there may be local pain, bruising or phlebitis. Collections of nasopharyngeal swab samples may also incur discomfort, which is transient and of moderate intensity. In order to mitigate risks inherent to these procedures, the collections will be carried out by a trained health professional, as designated by the research center (for the baseline exams) and by a trained team designated by the coordinating center to collect the other exams.

There are potential risks related to the use of halofuginone. The main risks are gastrointestinal symptoms such as nausea and vomiting, as well as fatigue. Regarding nausea and vomiting, antiemetics will be prescribed and provided free of charge to patients, following the guidelines of the protocol. Another potential risk of the use of halofuginone refers to a greater chance of bleeding, however, this risk is mitigated by clear and specific criteria and exclusion, not allowing the inclusion of patients with a high risk of bleeding in the study.

## **8.5 Benefits for Participants**

Currently, the benefits of treating SARS-CoV-2 with halofuginone are potential, but unknown. Due to its mechanism of action, halofuginone has the potential to be effective in treating patients with COVID-19, decreasing viral replication and potentially preventing severe forms of the disease. If it proves to be effective, treatment can contribute to better clinical outcomes of the disease in patients in the intervention group.

Research participants will receive the results of laboratory tests collected by the research protocol via specific link protected by password, individual and secure that will be sent via email and telephone message.

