### *3.8.2 Day 5 – At home*

- Collection of nasopharyngeal swabs for SARS-CoV-2;
- Collection of blood tube for analysis of serum level of halofuginone.

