### 3.9 Allocation concealment and randomization

Patients will be randomized in the proportion of 1:1:1, for the control arms, halofuginone 1mg and halofuginone 0.5mg. The randomization list will be generated electronically by an independent statistician using a specific software. Randomization will be performed in blocks and will be stratified by age (<60 years and ≥ 60 years).

The allocation concealment of the randomization list will be maintained through an automated and centralized randomization system accessed via the internet, available 24 hours a day. Patients who do not meet the eligibility criteria to participate in the study should not be recruited and randomized, and this will be considered a violation of the protocol. Patients, principal investigators and local staff will be kept blind to the allocation; only the sponsor will be aware of the blinding codes. The assessors and statisticians responsible for the results will be kept blind in relation to the allocated treatments.

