### 3.10.5 Coding of study medication

Solutions with two different concentrations of halofuginone (0,5mg/5mL e 1 mg/5 mL) and a placebo solution will be used.

Each individual treatment solution will be identified by one of three random letters (from A to I) unique to each group. The code list will be sequential and unknown to researchers and patients, which the codes will be known exclusively by the pharmacist responsible for the study.

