### 3.11 Collection, use and storage of biological material

#### 3.11.1 *Blood Tests*

Collections of the following blood laboratory tests will be performed on the day of inclusion in the study (baseline) and on the tenth day: CBC, urea, creatinine, alkaline phosphatase, gamma-GT, aspartate aminotransferase, alanine aminotransferase, direct and indirect bilirubin, C-reactive protein , prothrombin time with INR, activated partial thromboplastin time, fibrinogen, sodium, potassium and a tube for serum analysis of the study drug (will also be collected on the fifth day). Baseline exams will be collected by trained staff from the participating center and 10th day exams will be collected by trained technical staff at the patient's home.

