#### *3.11.4 Locals for processing, storage and performance of laboratory tests*

The biological samples will be sent to the Central Laboratories daily. The Central Laboratories are the Clinical Laboratory of Hospital do Coração, DASA and the Laboratório de Investigações Médicas da Faculdade de Medicina da USP. The biological samples will be processed and analyzed at these laboratories. The routine tests will be performed at the DASA and at the Hospital do Coração; the serum dosage of Halofuginone will be performed at the Laboratório de Investigações Médicas da Faculdade de Medicina da USP and the assessment of SARS-CoV-2 viral load will be performed at Clinical Laboratory of Hospital do Coração. The storage of biological samples will be transient, for enough time to perform all the analyses, as necessary, and they will be destroyed according to Good Laboratory Practices.

All Central Laboratories have adequate infrastructure to develop this research protocol, as refrigerators with strict temperature control, restricted access and monitored by cameras 24 hours a day, 7 days a week. The staff involved on laboratory analyses is trained to perform its activities.

All biological material will be used exclusively for the purposes provided for in this protocol, in accordance with the provisions of Resolução CNS No. 441/2011 and Portaria No. 2.201/2011 and in compliance with the consent obtained from the research participants. There is no intention for future research using the biological samples collected in this study.

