| Clinical and safety data via
phone call            |   |   |   |   |    |   |   |   |   |   | X | X |

\* Only serum level of halofuginone

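### Section 8.5 promises participants their laboratory results without excepting the serum halofuginone level, so a patient could be unblinded while still reporting symptoms and adverse events

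*Protocol*

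**What the plan says.** **Release of results.** Section 8.5 of the protocol lists among the benefits: "Research participants will receive the results of laboratory tests collected by the research protocol via specific link protected by password". The link goes out by email and telephone message. No test is excepted and no date of release is given.

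**What counts as a laboratory test.** Table 4 has a laboratory-tests row with entries at Day 1, Day 5 and Day 10. The Day 5 entry carries the footnote "Only serum level of halofuginone". Section 3.11.1 introduces a list of blood laboratory tests and ends it with "potassium and a tube for serum analysis of the study drug (will also be collected on the fifth day".

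**Where the level is kept apart.** The synopsis gives the drug-level tube its own sentence after the list of tests. Section 3.8.2 lists it as "Collection of blood tube for analysis of serum level of halofuginone", and section 3.8.3 gives it a bullet separate from the laboratory tests. Section 3.11.4 sends the routine tests to two laboratories but says "the serum dosage of Halofuginone will be performed at the Laboratório de Investigações Médicas da Faculdade de Medicina da USP".

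**Blinding and codes.** Section 3.9 keeps patients, investigators and local staff blind, and also the outcome assessors and statisticians. It adds that "only the sponsor will be aware of the blinding codes". Under section 3.10.5 each solution is "identified by one of three random letters (from A to I) unique to each group", and "the codes will be known exclusively by the pharmacist responsible for the study".

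**The concern.** A serum level of the study drug comes close to revealing the allocation. If the results link carries it, a participant learns whether they are on active drug or placebo, although section 3.9 says they must not.

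At stake are the outcomes that depend on what the patient says or does:

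- time to symptom resolution, from the daily questionnaire to Day 10;
- the split between limited and unlimited activities at the mild end of the Day 14 scale;
- low-grade adverse events and minor bleeding, reported to Day 28;
- discontinuation of study drug.

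In a placebo-controlled trial, knowledge of allocation can bias these in either direction. This is not a detail that a protocol leaves to the analysis plan. It is a participant entitlement written into the protocol that, followed as worded, works against another rule in the same document.

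A lesser matter is how far a broken code reaches when several patients share one letter.

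**Working it through.** The plan gives no figure to reproduce. The check is a reading of the text, with two small calculations.

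**1. Does the text release the level?** Section 8.5 covers laboratory tests collected under the protocol. Table 4 and section 3.11.1 count the drug level among them, and on Day 5 it is the only one. The synopsis and sections 3.8 and 3.11.4 list it separately, but none says the result is withheld from participants or sites. The literal reading therefore releases it, and nothing in the protocol stops that.

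**2. Would a level reveal the arm?** Inputs from Table 3 (section 3.10.4):

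| Dose | Cmax (ng/mL) | Tmax (h) | T½ (h) |
|---|---|---|---|
| 0.5 mg | 0.54 | 2.8 | 17.2 |
| 1 mg | 0.88 | 2.0 | 31.5 |

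Assume first-order decay from the peak. The level 24 h after a dose is Cmax × 2^(−(24 − Tmax)/T½).

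- 0.5 mg: 0.54 × 2^(−21.2/17.2) = 0.54 × 0.426 = 0.23 ng/mL
- 1 mg: 0.88 × 2^(−22/31.5) = 0.88 × 0.616 = 0.54 ng/mL

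If the Table 3 peaks are single-dose values, daily dosing multiplies these by 1/(1 − 2^(−24/T½)).

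- 0.5 mg: factor 1.61, trough about 0.37 ng/mL
- 1 mg: factor 2.44, trough about 1.32 ng/mL

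The range at the end of a dosing interval is thus 0.23 to 0.37 ng/mL (0.5 mg) and 0.54 to 1.32 ng/mL (1 mg), with zero expected on placebo. A level separates active from placebo, provided the assay detects such concentrations; its limit is not stated. It need not separate the two doses in an individual.

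**3. When would it matter?** Section 3.11.4 sends samples to the laboratories daily, but no assay turnaround and no release date are given. By time of release:

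| Result reaches the patient | Reports still to come |
|---|---|
| Between Day 5 and Day 10 | remaining daily symptom reports, discontinuation, Day 14 and Day 28 calls |
| Between Day 10 and Day 14 | Day 14 scale, symptoms and adverse events; Day 28 adverse events |
| Between Day 14 and Day 28 | Day 28 adverse events |
| After Day 28 | none |

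**4. The letters.** Read as three letters per arm from A to I, there are 9 letters for 150 patients: 150/9 = 16.7, about 17 per letter, a third of an arm. With 2 to 5 hospitals and, as an assumption, equal enrolment, a site has about 17/5 ≈ 3 to 17/2 ≈ 8 patients with a given letter.

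**The case against.** The strongest reply is that the authors meant routine safety tests only. The synopsis, the visit lists and the separate assay laboratory point that way, and section 3.9 expressly requires patients to stay blind. On this view the defect is a missing exemption, not a planned disclosure. That stands as to intent. It does not settle what a results portal built from section 8.5 and Table 4 would send.

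Four stronger readings are tempting, and the protocol does not support them.

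- **All 150 participants will be unblinded during follow-up.** Release after Day 28 is as consistent with the text as release on Day 6. Up to 150 is also a ceiling, because section 3.10.3 stops laboratory collection once treatment is interrupted.
- **The primary result is compromised.** The viral-load slope is a laboratory measure and is little exposed to a patient's knowledge of allocation.
- **Sections 3.9 and 3.10.5 contradict each other on who holds the codes.** Section 3.10.7 places the pharmacist at the coordinating centre, and section 12 treats sponsor and coordinating centre as one. The pharmacist is most naturally the sponsor's code holder. Since section 3.9 keeps assessors and statisticians blind, nothing shows that analysis or assay staff hold the codes. The wording is loose, no more.
- **One code break unblinds 17 patients.** It informs only people who know which others carry that letter. A patient who sees a drug level learns only their own arm. Staff at one site could infer the arm of perhaps 3 to 8 patients; reaching all 17 needs information to pass between sites.

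Nor is there a case here for withholding viral loads from the coordinating team. Nothing shows that a viral load reveals the arm, and the synopsis has the monitoring committee assess primary outcomes at 60 patients.

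**Conclusion.** The point holds as a gap between section 8.5 and the blinding rule in section 3.9. The protocol promises laboratory results without exception or delay, classes the drug level as a laboratory test in two places, and nowhere withholds it. A released Day 5 or Day 10 level would tell a patient whether they take active drug or placebo.

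This rests on three assumptions: that the literal reading of section 8.5 is the one followed, that the assay detects levels of roughly 0.2 to 1.3 ng/mL, and that results go out before the Day 28 call. The first is open, because other sections treat the level separately. The second is likely, since measuring the drug is what the assay is for. The third is not stated either way. The leak is therefore possible rather than certain. It bears on patient-reported secondary and safety outcomes and hardly on the primary one. It deserves correction because the remedy is so small.

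The shared letters and the loose wording on the code holder are secondary.

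**What to change.** **Main change.** Add to section 8.5 and to the consent form: halofuginone concentrations are not released to participants, sites, or blinded assessors and statisticians until database lock and unblinding. Routine safety results are still released as promised. Emergency code breaks and the monitoring committee's access are unchanged. Then make Table 4, section 3.8 and section 3.11.1 agree on whether the drug level is a laboratory test.

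*Cost:* one sentence in two documents and a filter on the results link. Participants wait for one result.

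**Secondary changes.**

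- Replace the nine shared letters in section 3.10.5 with participant-specific bottle numbers, for bottles not yet dispensed. *Cost:* relabelling.
- Align sections 3.9 and 3.10.5 so that both name the coordinating-centre pharmacist as the sponsor's code holder, and check that this fits the emergency procedure in section 3.10.6, which runs through the coordinating centre. *Cost:* a wording change.

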## 8.6 Reporting adverse events

### 8.6.1 *Adverse Events (AE)*

An adverse event (AE) is any unfavorable medical occurrence in a clinical study participant who has been administered a drug and who does not necessarily have a causal relationship to treatment. An AE can, therefore, be any unfavorable and/or unintended sign, symptom or disease, temporarily associated with the use of a study drug, and whether or not considered to it. AEs may also include pre- or post-treatment complications that occur as a result of procedures specified in the protocol, lack of efficacy, overdose, reports of drug abuse/misuse or professional exposure. Pre-existing events that increase in severity or change in nature during or as a result of participating in the clinical study will also be considered AEs.

An AE does not include the following:

- Medical or surgical procedures, such as surgery, endoscopy, tooth extraction and transfusion. The condition that led to the procedure can be an adverse event and must be reported.
- Pre-existing diseases, conditions or laboratory abnormalities present or detected before entering the study that do not get worse
- Situations in which an undesirable medical event has not occurred (for example, hospitalization for elective surgery, social and/or convenience admissions)
- Overdose without clinical sequelae
- Any medical condition or clinically significant laboratory abnormality with a start date prior to the date of signing the consent form, and not related to a procedure associated with the protocol. It is considered pre-existing and must be documented in the medical history and CRF

All adverse events must be recorded by the investigators on the clinical records (CRF), regardless of severity.

### 8.6.2 *Serious Adverse Events (SAE)*

All serious adverse events (SAE) should be recorded by the investigators on the clinical records (CRF) within a maximum of 24 hours from the moment the investigator became aware of the event. Serious adverse event is the one that results in any adverse experience with drugs, biological products or devices, occurring at any dose and that results in any of the following outcomes:

- a) death;
- b) threat to life;
- c) persistent or significant incapacity/disability;
- d) requires hospitalization or prolongs hospitalization;
- e) congenital anomaly or birth defect;
- f) any suspicion of transmission of an infectious agent by means of a drug or;
- g) clinically significant event.

The principal investigator at the research center is responsible for informing research ethics committees of any serious adverse events as required by local regulations within 24 hours.

The HCor Research Institute is responsible for receiving and monitoring all adverse events that occurred during the clinical study. All adverse events classified as serious according to the definition of RDC 09/15 must be informed to the sponsors within a maximum period of 24 hours through the specific email and the Serious Adverse Event Notification Form, according to RDC 09/15.

The causal relationship of all adverse events (serious and non-serious) with the products under investigation (Halofuginone or placebo) is characterized as follows:

- Related: There is clear evidence that the event is related to the use of the products under investigation.
- Possible: The event cannot be explained by the clinical condition of the research participant, concomitant therapy, or other causes, and there is a plausible temporal relationship between the event and the administration of the products under investigation.

- **Improbable** An event for which an alternative explanation is more likely (e.g., concomitant medications or ongoing clinical conditions), or the temporal relationship to exposure to products under investigation suggests that a causal relationship is unlikely.
- **Not Related:** The event can be explained immediately by the research participant's underlying clinical condition, concomitant therapy, or other causes.

Data regarding security outcomes of interest will be collected as described in section **4.3**.

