### *3.8.4 Day 14 and day 28 - follow-up via phone call*

- Telephone follow-up to collect clinical data.
- At the follow-up visit on the day 14, information on the patient's status will be requested on the ordinal symptom scale (1. not hospitalized, without limitation of daily activities; 2. not hospitalized,

with limitation of daily activities; 3. hospitalized, unnecessary of supplemental oxygen; 4. hospitalized, requiring supplemental oxygen; 5. hospitalized, requiring high-flow nasal oxygen therapy, non-invasive mechanical ventilation, or both; 6. hospitalized, requiring blood oxygenation through a membrane system (ECMO), invasive mechanical ventilation, or both; 7 Death), presence of symptoms (myalgia, fever, shortness of breath, cough, diarrhea, nausea, vomiting and headache) and presence of adverse events (bleeding or other adverse events or symptoms reported by the patient).• At the follow-up visit on the day 28, information on vital status, need for hospitalization, need for invasive mechanical ventilation (in case of hospitalization) and presence of adverse events (bleeding or other adverse events or symptoms reported by the patient) will be requested.

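### The Possible causality class in section 8.6.2 excludes events that drug and illness could both explain, so drug-related nausea and vomiting are likely to be under-attributed

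*Protocol*

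**What the plan says.** Protocol section 8.6.2 sets one scale for the whole trial: "The causal relationship of all adverse events (serious and non-serious) with the products under investigation (Halofuginone or placebo) is characterized as follows". It has four classes.

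- Related: "Related: There is clear evidence that the event is related to the use of the products under investigation".
- Possible: "Possible: The event cannot be explained by the clinical condition of the research participant, concomitant therapy, or other causes", and in addition the timing relative to dosing must be plausible.
- Improbable: "An event for which an alternative explanation is more likely (e.g., concomitant medications or ongoing clinical conditions"), or the timing makes a causal link unlikely.
- Not Related: "The event can be explained immediately by the research participant's underlying clinical condition, concomitant therapy, or other causes".

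Two other sections show which events this scale will often have to handle. On the drug, section 8.4 states: "The main risks are gastrointestinal symptoms such as nausea and vomiting, as well as fatigue". On the patients, the day 14 call in section 3.8.4 asks about "presence of symptoms (myalgia, fever, shortness of breath, cough, diarrhea, nausea, vomiting and headache").

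**The concern.** A four-step causality scale needs a class for the ordinary ambiguous case, in which the timing fits the drug but the disease under treatment could also be the cause. One would expect Possible to be that class. Here it is closed to such events, because it requires that nothing else can explain them. Not Related is open to them, because it requires only an immediate alternative explanation and is silent on whether the drug is also a candidate.

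The ambiguous case should be common in this trial. Participants are outpatients with symptomatic COVID-19, and two of the drug's main expected toxicities are also symptoms that the protocol tracks in them. At stake is the accuracy of the relationship label in the safety record of a phase 2 trial. The label is assigned when the event is assessed, so a later analysis cannot readily recover a category that was never offered.

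**Working it through.** The protocol states no figure on this point and no arithmetic applies. The check sets the four definitions side by side and runs typical events through them.

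**What each class demands**

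| Class | Condition on other explanations | Condition on the drug |
|---|---|---|
| Related | none stated | clear evidence |
| Possible | none may exist | plausible timing |
| Improbable | one is more likely (or timing is against the drug) | none further |
| Not Related | one explains the event immediately | none |

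**Event A: new nausea, plausible timing, drug and illness about equally likely**

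1. Related fails: equal plausibility is not clear evidence.
2. Possible fails its first condition: the illness can explain the event.
3. Improbable fails: the alternative is not more likely, and the timing is not against the drug.
4. Not Related fits if the assessor judges that the illness explains the nausea immediately. Otherwise no class fits.

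**Event B: as A, but the illness is somewhat more likely**

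Improbable fits. Not Related may fit as well, so the two lower classes overlap. Possible stays closed.

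**Event C: nausea closely following doses**

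Section 3.10.4 reports that in the cited phase I study most patients' symptoms began 30 to 60 minutes after dosing. A clear pattern of that kind could support Related, which has no exclusion clause.

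**Event D: plausible timing and no other explanation**

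Possible fits. This is the only kind of event it accepts.

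The scale thus works at its two ends (C and D on one side, a clearly likelier alternative on the other) and fails in the middle (A). The wording pulls A downwards.

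**Which events are affected**

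- Nausea and vomiting: drug risks in section 8.4 and tracked symptoms in section 3.8.4. Section 3.10.2 also names nausea among the symptoms that standard COVID-19 care may treat. The overlap is documented.
- Fatigue: a drug risk in section 8.4, but absent from the symptom list in section 3.8.4. The protocol does not document the overlap.
- Symptoms present at entry that do not worsen: not adverse events under section 8.6.1, so they never reach the scale.

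**How often**

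Table 1 (section 3.10.4) gives, for the first two-week cycle, nausea in 3 of 4 and vomiting in 2 of 4 patients at 1 mg/day, and 1 of 5 and 2 of 5 at 0.5 mg/day. These show that the events are to be expected. They come from 9 cancer patients (4 + 5) and are incidences, not misclassification rates, so they do not measure the fault.

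**The case against.** The strongest case against the point is that little depends on the label.

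- Safety outcomes I to III in section 4.3 count new graded adverse events, bleeding and serious adverse events without regard to causality.
- Section 8.6.2 sends serious events to ethics committees and sponsors whatever their attribution, and section 8.6.1 has all adverse events recorded.
- The interim safety review in section 6.2 compares adverse events between arms, again with no causality filter.

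All of this stands. A reader might infer that related events are under-reported to ethics committees, the sponsor or the monitoring committee. The protocol does not support that: no event goes unreported because of this wording.

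A reader might also infer that safety outcome IV is distorted. Its wording is ambiguous: the phrase about being drug-related sits with treatment rather than with discontinuation, and may mean no more than stopping the study drug. Nothing ties it to the scale in section 8.6.2, so that link is not established.

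A third objection is that attribution is made blind (section 3.9), so the wording acts alike in all arms. That rules out differential judgement. It does not restore the label: true drug effects arise only in the active arms, and those are the events that lose it.

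**Conclusion.** The point holds as a drafting fault in the causality scale. Possible leaves no place for an event that both drug and COVID-19 could cause, and such events tend to be labelled Improbable or Not Related. Under-attribution of drug-related nausea and vomiting in the causality record is therefore likely. Its size cannot be derived from the protocol.

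The conclusion assumes that assessors apply the definitions as written and that ambiguous nausea and vomiting do occur.

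It would go too far to say that all such events, or fatigue as well, will be classed as unlikely or unrelated. Related remains open where dose timing gives clear evidence, Not Related requires an immediate alternative explanation, and some events fit no class at all. For fatigue, the protocol does not show that it is also a symptom of the illness.

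The effect stops at the label. Total counts by arm, serious-event reporting and the monitoring committee's comparison stand. The protocol plans no tabulation by relationship, but any made later would inherit the fault. The change is worth making because the rule mislabels events when followed and costs almost nothing to correct.

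**What to change.** Reword two definitions in section 8.6.2:

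- Possible: the timing is plausible and the event could be due to the product, although the disease or another treatment may also explain it.
- Not Related: there is no plausible relationship between the event and the product.

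Related and Improbable can stay. The revised Possible then takes the balanced case, and Improbable takes the case where the alternative is more likely. Align the matching eCRF text.

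The cost is the rewording itself. Design, sample size and comparisons by arm are untouched. The small downside is that more events will be labelled possibly related in every arm, placebo included, so the label should be read against the placebo rate.
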